| Statistical Methods:  Statistical Methods (cont’d.) | Demography: descriptive statistics will be provided.  Vaccine reactogenicity: Analyses concern graded severities for local and systemic reactogenicity: Comparing one group with another during a treatment period (the design has two periods following the first and second test article exposures), these are two-sample, cross-sectional comparisons of binary, ordinal, or continuous data. Comparing a group with itself between periods, these are paired, repeated measures data. Two-sample, cross-sectional comparisons are based on Fisher’s exact and Cochran-Mantel-Haenszel tests for binary and ordinal outcomes, respectively. Student’s-t and Wilcoxon tests are used for continuous outcomes. These methods permit statistical tests to address the following topics:   - 1. comparison of active and placebo after test article dose 1   2. comparison of active and placebo after test article dose 2, with and without testing for the impact of, and adjustment for, outcomes after dose 1   3. comparison of active and placebo in successive test article doses   4. comparison of placebo in successive test article doses   5. comparison of change from active to active with change from placebo to placebo   Items c. and d. are paired comparisons, which may be performed by McNemar tests or, more flexibly, by GEE models with a binary or continuous outcome. Items b. and e. are tests of interaction: dose 1 by dose 2 in item b., and period by vaccine in item e. and also accessible by GEE models.  Adverse events: Adverse events will be tabulated by body system using the COSTART dictionary, by severity, by seriousness, by relationship to study drug, and by elapsed time since last exposure to study drug. This yields primarily binary data (for each subject, the given COSTART event did or did not occur) which may be analyzed in the same manner as the binary reactogenicity events.  Vital signs & clinical laboratory measures: Mean values and S.D.s will be plotted separately by treatment group. Extreme values and/or outliers will be discussed individually. For clinical laboratory measures within cross-over groups, quantitative outcomes at baseline and day 28 will be compared by paired Student’s t-tests and Wilcoxon signed rank tests. Binary outcomes will be compared by McNemar’s tests.  Immunogenicity: Immunogenicity measures will include serum hemagglutination-inhibiting (HAI) antibody titers specific for the strains included in the vaccine, levels of secretory IgA (sIgA) specific for these viruses in nasal wash fluids. For the HAI titers, analyses will concern geometric mean titers (GMT), proportions of subjects with titer ≥ 40, and proportions with  four-fold increase over baseline. For specific sIgA levels, analyses will concern geometric means and fold-rise from baseline. HAI GMTs and geometric mean nasal specific sIgA levels will be accompanied by 95% confidence intervals. Comparing active-to-placebo and active-to-active groups, titers/antibody levels will be contrasted on day 28 by t-tests on log10(titer). Within the groups, paired tests will be used (Student’s t and Wilcoxon signed rank). Fold-rises may be examined with and without covariate-adjustment for previous titers. Without such adjustment, there are two binary fold-rise outcomes, and these are compared within and between groups by chi-square and stratified chi-square tests. (In the latter case, 2 x 2 tables of treatment by outcome are stratified by previous titers.) With covariate adjustment, the fold-rise outcome is the log10-ratio of early and later titers. Adjustment after the first treatment is for pre-treatment titer and adjustment after the second treatment is for both baseline titer and for titers after the first treatment.  Response to viral challenge: The analysis concerns between-group comparisons of the three groups regarding clinical and immunologic binary outcomes. Alternative definitions provide six binary clinical outcomes that can be compared between groups by chi-square tests. More flexible analyses use logistic regression (with the presence or absence of illness, separately for each definition, as the outcome. Covariates are cross-over study group, age, gender, race, and, for some models, titers after vaccinations 1 and 2.  Additional analyses will be based on illness score and on virus shedding assessed by two methods: peak and a time-weighted average calculated as a trapezoidal-rule AUC. For both peak and AUC, viral shedding is in units of log10(titer). These continuous data will be compared between cross-over groups by Student’s t-tests and Wilcoxon tests and, in a more flexible analysis, by linear model adjusted for the demographic and clinical covariates cited above.  Finally, the three binary measures of influenza and the two viral load estimates (peak titer and AUC) will be assessed relative to the two immunologic measures, HAI reciprocal titer and nasal secretory IgA. For the binary measures, mean viral load (for each measure) is compared by t-tests between those with and without influenza (for each definition). For the two immunologic measures, the test of association with viral load will be based on Pearson correlations of log-titers. |

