Immunogenicity data have been consistent, particularly for the influenza A components. Between 40 and 60% of subjects entering the trials with serum hemagglutination inhibition (HAI) reciprocal titers < 40 for a given virus (a level typically associated with susceptibility) have demonstrated HAI titer rises of ≥ 4-fold and/or attained reciprocal titers ≥ 40. In unselected populations, HAI reciprocal titers ≥ 40, a four-fold rise, or both are seen in between 70 and 100% of subjects after immunization with any regimen containing at least 15 μg of influenza HA. Geometric mean nasal secretory IgA (sIgA) levels specific for the vaccine virus strains rise between two- and four-fold after immunization. Nasal sIgA responses tend to be stronger following two-dose regimens (3 to 4 –fold) than one-dose regimens (1.8 to 3-fold), but are statistically significant in almost all cases by repeated measures analysis of variance. These immune response levels are equal or superior to published responses to live, cold-adapted nasal influenza vaccines which have proven efficacious in the field.

As noted by Beyer *et al*., both increased serum HAI titers and specific nasal wash secretory IgA have been associated with protection against influenza (19). The relative importance of these factors in the induction of protection by non-living mucosal vaccines remains to be fully defined, rendering protective efficacy difficult to predict from immunogenicity data alone. Intranasal challenge of healthy young adults with egg-grown virulent influenza virus has been used extensively and safely in the United States and the United Kingdom to evaluate the immunogenicity and protective potential of a variety of live single-gene reassortant and subunit vaccine candidates (41, 42), to characterize the efficacy of the live, cold-adapted vaccine candidate and compare it to the intramuscular vaccine (43 – 45), and to test anti-viral compounds (46, 47).

Recently, ID Biomedical has collaborated with Retroscreen Virology limited to conduct a challenge study in subjects immunized intranasally with FluInsure™ or saline placebo. FluInsure™ regimens in this randomized, double-blinded study included either one or two intranasal doses of vaccine delivering 30 μg of each influenza HA (with an approximate four-fold excess of proteosome proteins). These subjects were subsequently challenged intranasally with egg-grown A/Panama/2007/99, the current A/H3N2 strain.

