- A  4-fold increase in serum A/Panama/2007/99 HAI antibody titer between day 39 ( 3) and the final follow-up visit, and absent clinical disease suggesting influenza between discharge from the isolation unit and the final follow-up visit.

9.3.7 Laboratory-confirmed Influenza Illness:

A subject will be deemed to have laboratory-confirmed influenza illness if he/she meets the definitions for BOTH of:

- Influenza infection, and
- Illness (Any).

9.3.8 Analysis:

9.3.8.1 Power Considerations:

The analysis will consider both binary outcomes (e.g., illness vs. no illness; virus shedding vs. no virus shedding, etc.) and continuous outcomes (e.g., treatment group mean temperatures, tissue counts, peak viral shedding and shedding AUC, etc.). The variability, and potential magnitudes of the differences in the latter are *a priori* unknown. However, the virus challenge inoculum will be selected to yield *approximately* 50 - 60%, based on past experience, of the binary outcome “any illness.” (Closer control of this rate is difficult to ensure.) Assuming that a minimal efficacy level of 70% (where efficacy = [rate controls -ratetreated ] x 100 / rate controls) is of interest to justify further development of a given dose or formulation, it is possible to calculate that a group size of 28 will yield ≥ 0.80 power to detect a ≥ 70% reduction in the rate of the binary outcome “any illness.”

9.3.8.2 Analyses:

The analysis concerns between-group comparisons of the four cross-over groups regarding clinical and immunologic binary outcomes. Alternative definitions provide six binary clinical outcomes (fever, upper respiratory illness, lower respiratory illness, systemic illness, illness [any], and illness + infection) that can be compared between groups by chi-square tests. More flexible analyses use logistic regression (SAS PROC LOGISTIC) with the presence or absence of influenza, separately for each definition, as the outcome. Covariates are cross-over study group, age, gender, race, and, for some models, titers after vaccinations 1 and 2.

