Additional secondary analyses will be based on tissue counts (and weights, if feasible) as a marker of illness severity, and on virus shedding assessed by two methods: peak and a time-weighted average calculated as a trapezoidal-rule AUC. For both peak and AUC, viral shedding is in units of log10 (titer). These continuous data will be compared between cross-over groups by Student’s t-tests and Wilcoxon tests and, in a more flexible analysis, by linear model adjusted for the demographic and clinical covariates cited above.

Finally, the three binary measures of influenza and the two viral load estimates (peak titer and AUC) will be assessed relative to the two immunologic measures, HAI reciprocal titer and nasal secretory IgA. For the binary measures, mean viral load (for each measure) is compared by t-tests between those with and without influenza (for each definition). For the two immunologic measures, the test of association with viral load will be based on Pearson correlations of log-titers.

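### Section 9.3.8.2 announces a comparison of influenza illness with HAI and nasal sIgA, but the test it prescribes for illness uses viral load and contains no antibody measure

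*Protocol*

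**What the plan says.** Section 9.3.8.2 ends with an analysis linking outcome to immune response. Its opening sentence takes three binary influenza measures, which it does not name, together with peak viral titer and viral AUC, and states that they "will be assessed relative to the two immunologic measures, HAI reciprocal titer and nasal secretory IgA".

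Two methods follow. For illness: "For the binary measures, mean viral load (for each measure) is compared by t-tests between those with and without influenza". For antibody: "For the two immunologic measures, the test of association with viral load will be based on Pearson correlations of log-titers". The statistical methods in the synopsis prescribe the same test for illness: "For the binary measures, mean viral load (for each measure) is compared by t-tests".

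Earlier in 9.3.8.2, illness under each definition is modelled by logistic regression, where "Covariates are cross-over study group, age, gender, race, and, for some models, titers after vaccinations 1 and 2". That part of the section also states: "Alternative definitions provide six binary clinical outcomes", and it lists them.

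Section 7.2.6 sets the sampling times. Serum for HAI is taken at the first screening visit and on Immunization Phase Day 0; nasal wash for sIgA is taken at the second screening visit. Both are then taken on Immunization Phase Day 28, Challenge Phase Day 0 and Challenge Phase Day 20–30. Dosing is on Days 0 and 14.

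**The concern.** The announcing sentence and the method sentence do not describe the same analysis. A reader expects antibody to be compared between subjects with and without influenza and finds viral load compared instead. This goes beyond detail left to a SAP: the protocol does specify a test, and the test holds the wrong variable for its stated purpose. A SAP that followed the text faithfully would carry the mismatch forward.

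The pairing matters to the protocol's own argument. On serum HAI and nasal sIgA, section 1.0 says: "The relative importance of these factors in the induction of protection by non-living mucosal vaccines remains to be fully defined". It adds that efficacy is therefore hard to predict from immunogenicity data alone.

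The correlations of antibody with viral load do not fill the gap. Section 1.0 describes vaccine-induced serum antibody as important for preventing illness but rather ineffective against infection itself or the duration of shedding. It also reports poor culture sensitivity for this challenge strain. An antibody could therefore protect against illness while correlating only weakly with measured shedding.

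**Working it through.** The plan gives no figure for this analysis, so there is none to reproduce. The check is to set what is announced beside what is prescribed.

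**Step 1. Pairings announced and tested in the closing paragraph of 9.3.8.2**

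| Pairing | Announced | Test given in that paragraph |
|---|---|---|
| Viral load × HAI | yes | Pearson correlation |
| Viral load × sIgA | yes | Pearson correlation |
| Illness × HAI | yes | none |
| Illness × sIgA | yes | none |
| Illness × viral load | no | t-test |

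Two of the four announced pairings have a test. The t-test belongs to a fifth pairing that was not announced.

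**Step 2. Do the logistic models supply the two missing pairings?** In part.
- The titer covariates enter only some of the models, and the protocol does not say which.
- sIgA is not expressly named. Section 9.1 mostly writes of HAI titers and sIgA levels, but it also applies log10(titer) to both assays, and 9.3.8.2 speaks of log-titers for both. The word alone does not decide the matter.
- One of the two covariates cannot be built. Section 7.2.6 schedules no serum or nasal wash between the doses on Days 0 and 14, so there is no separate titer after vaccination 1.

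**Step 3. Is a suitable pre-challenge sample available?** Yes. Sections 7.1.10 and 7.2.6 schedule both serum and nasal wash on Challenge Phase Day 0. The inoculum is given on Challenge Phase Day 2, two days later.

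**Step 4. What could the missing comparison detect?** This is an illustration for any illness, with about 25 challenged per group (section 4.1) and two-sided alpha 0.05 (section 9.0). The illness rates are assumptions:
- placebo 55%, the middle of the 50–60% in 9.3.8.1;
- one-dose group 45%, close to the 45.8% reported for one dose in section 1.0;
- both two-dose groups 16.5%, which is 0.55 × (1 − 0.70).

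Expected ill = 25 × (0.55 + 0.45 + 0.165 + 0.165) = 33.25, or about 33 of 100, leaving 67 not ill.

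Detectable standardized difference in log antibody at 80% power, unadjusted:
(1.96 + 0.842) × √(1/33 + 1/67) = 2.802 × 0.2127 = 0.60 SD.

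Range, for placebo illness of 50% or 60% and the same efficacy of 0% or 70% in all three active groups:

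| Placebo rate | Efficacy | Ill / not ill | Detectable SD |
|---|---|---|---|
| 50% | 0% | 50 / 50 | 0.56 |
| 50% | 70% | 23.75 / 76.25 | 0.66 |
| 60% | 0% | 60 / 40 | 0.57 |
| 60% | 70% | 28.5 / 71.5 | 0.62 |

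A treatment-group term raises these values by roughly 1/√(1 − R²), where R² is the share of antibody variance explained by group. R² is not given in the protocol. If it is assumed to lie between 20% and 50%, 0.60 becomes 0.60/√0.80 = 0.67 to 0.60/√0.50 = 0.85 SD.

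**The case against.** The strongest reply is that the logistic models already have the needed form: illness under each definition, with study group and post-vaccination titers as covariates. If titers is read broadly, as 9.1 and 9.3.8.2 permit, sIgA is included and only the wording is loose. It can be added that relating immune response to protection is not among the objectives in section 2.0. The paragraph comes last, after analyses the protocol itself calls secondary, and section 9.0 says the trial will not provide definitive evidence of efficacy.

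Much of this stands, and it bounds the point. A reader might infer that illness is never examined against sIgA, or that the whole question goes unanswered. The text does not support that: viral load is tested against both antibodies, illness against HAI is reachable through the logistic models, and illness against sIgA arguably is too. What remains is that the dedicated paragraph prescribes a test that cannot deliver what it announces, while the fallback is optional, does not expressly name sIgA and depends partly on a sample that is not taken.

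A reader might also infer that the three binary measures are a miscount of the six clinical outcomes listed earlier in 9.3.8.2. That is not shown. Three could equally mean any illness, infection and laboratory-confirmed illness (9.3.5 to 9.3.7), and infection on its own is not among the six. The protocol leaves the three unnamed, so this needs clarifying and should not be corrected by guesswork.

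**Conclusion.** The point holds as a mismatch between a stated aim and its prescribed test, present in both section 9.3.8.2 and the synopsis. Neither illness pairing has a test in the paragraph that announces it; elsewhere each depends on optional covariates, one of which cannot be constructed from the scheduled samples.

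The weight is moderate. No objective, sample size, efficacy comparison or data collection changes, but the text should be corrected before unblinding so that the antibody time point and the influenza definitions are not chosen after the data are seen.

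The 0.60 SD shows what an unadjusted comparison could detect under the assumed illness rates (0.56 to 0.66 over the range shown). It does not measure harm done by the present text. It refers to any illness; the other definitions will have different numbers of cases. With a group term the detectable difference is larger, by an amount the protocol gives no basis to fix.

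**What to change.** In section 9.3.8.2 and the synopsis:

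1. Add a comparison of log10 HAI titer and log10 nasal sIgA from the Challenge Phase Day 0 sample between subjects with and without influenza, by logistic regression of each binary measure on log antibody with a treatment-group term.
2. Keep the comparison of viral load between subjects with and without influenza, listed as a separate analysis. It is a legitimate question and should not be deleted.
3. Name the three binary influenza measures and reconcile them with the six outcomes listed earlier in the section.
4. In the logistic covariates, state whether sIgA is included, and remove or replace the titer after vaccination 1, for which no sample is scheduled.

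The cost is a few sentences and a few extra secondary models. Serum and nasal wash are already scheduled, so no visit, sample or assay is added. The extra tests add to a list that section 9.0 leaves uncorrected for multiplicity, and should be reported as exploratory.

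### The closing paragraph of 9.3.8.2 sets out to relate influenza outcomes to HAI and nasal sIgA, but the test it prescribes for them contains neither antibody

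*Protocol*

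**What the plan says.** The closing paragraph of Protocol 9.3.8.2 takes the binary influenza measures together with two viral-load summaries (peak and AUC) and states that they "will be assessed relative to the two immunologic measures, HAI reciprocal titer and nasal secretory IgA". Two tests follow.

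- For the binary measures: "mean viral load (for each measure) is compared by t-tests between those with and without influenza (for each definition").
- For HAI and sIgA: "the test of association with viral load will be based on Pearson correlations of log-titers".

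The synopsis, under Statistical Methods, gives the same first test: "mean viral load (for each measure) is compared by t-tests between those with and without influenza".

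Earlier in 9.3.8.2 the plan states: "Alternative definitions provide six binary clinical outcomes". These are fever, upper respiratory, lower respiratory and systemic illness, any illness, and illness plus infection. It continues: "More flexible analyses use logistic regression (SAS PROC LOGISTIC) with the presence or absence of influenza, separately for each definition, as the outcome". For these models, "Covariates are cross-over study group, age, gender, race, and, for some models, titers after vaccinations 1 and 2". The closing paragraph, by contrast, refers to three binary measures and does not say which.

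**The concern.** The aim and the test do not match. The aim pairs influenza status with antibody, whereas the test pairs influenza status with viral load. An analyst who follows the text would report how much virus ill and non-ill subjects shed. That is a reasonable question, but it is not the one announced.

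The announced question has value here. Section 1.0 says that the relative importance of serum HAI and nasal sIgA for protection by non-living mucosal vaccines is not yet fully defined, "rendering protective efficacy difficult to predict from immunogenicity data alone". A challenge study that measures both antibodies shortly before inoculation is well placed to add to this. This is also more than detail left to a statistical analysis plan: the protocol names a test, and the named test omits the variables of interest.

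**Working it through.** No arithmetic beyond counting is involved, and the plan gives no figure for this analysis to reproduce. The check sets the announced pairings against the prescribed tests.

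**1. Pairings in the closing paragraph**

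| Pairing | Announced? | Test given there? |
|---|---|---|
| Viral load with HAI | yes | yes, Pearson |
| Viral load with sIgA | yes | yes, Pearson |
| Influenza status with HAI | yes | none |
| Influenza status with sIgA | yes | none |
| Influenza status with viral load | no | yes, t-test |

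**2. Count.** If three binary measures are meant, 3 outcomes × 2 antibodies = 6 announced comparisons have no direct test in the paragraph, and 3 × 2 viral-load summaries = 6 t-tests stand in their place. If all six listed outcomes are meant, both counts are 6 × 2 = 12. The text does not say which reading applies.

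**3. Other analyses with influenza as the outcome.** The chi-square tests compare treatment groups and carry no antibody. The logistic models can carry titers, with four limits:

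- Titers enter only some models, and these are not identified.
- Study group is listed as a covariate with them. Vaccination is meant to raise titers, so a group-adjusted titer coefficient describes the association within groups. That is a different quantity from the overall association announced in the closing paragraph.
- sIgA is not named. Section 9.1 writes of titers and antibody levels as a pair when it means both measures, which suggests that titers alone means HAI. The closing paragraph of 9.3.8.2 does use log-titers for both, so this reading is likely but not certain.
- The covariates are described as titers after vaccinations 1 and 2. Sections 7.1.3, 7.2.6 and Table B.1 schedule serum on Immunization Phase Day 0 before dosing and next on Day 28; Challenge Phase Day 0 and Days 20–30 follow. Dose 2 is nominally on Day 14, so the first post-dose serum comes 28 − 14 = 14 days after dose 2. A titer after vaccination 1 alone is not collected.

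**4. Are the needed data available?** Yes. Sections 7.1.10 and 7.2.6 schedule serum for HAI and nasal wash for specific sIgA on Challenge Phase Day 0, two days before inoculation on Challenge Phase Day 2.

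**The case against.** The strongest reply is that 9.3.8.2 does relate influenza status to antibody, in the logistic models planned separately for each definition. This stands in part. A reader might infer from the closing paragraph that illness is never related to any immune measure, or that every outcome-by-antibody comparison is missing from the plan. The documents do not support that, because titers are named as covariates in some of those models and the synopsis says the same. If titers after vaccinations 1 and 2 is read collectively, the Day 28 or Challenge Phase Day 0 value could serve. What remains is that this cover is optional, group-adjusted and silent on sIgA, and that it does not repair a paragraph whose test contradicts its own aim.

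A second reply concerns importance. A correlate of protection is not among the objectives in section 2.0, the paragraph follows the secondary analyses, and section 9.0 says that the trial will not provide definitive evidence of efficacy or safety. This stands and limits the weight of the point.

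A reader might also call the viral-load t-test circular for illness plus infection. The overlap is only partial. Under 9.3.6, infection can be met by throat-swab detection or a four-fold HAI rise without nasal-wash shedding, and under 9.3.7 a subject who sheds without illness is not a case.

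Finally, one might object to Pearson correlation when some subjects shed no virus. How undetected virus is coded, and whether a rank correlation is preferred, are matters that a statistical analysis plan may settle. They form no part of this point.

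**Conclusion.** The point holds in limited form. In 9.3.8.2 and in the synopsis, the test prescribed for the binary influenza measures does not address the relation to HAI and sIgA that the same paragraph announces. The logistic models supply partial, optional cover for titers. A direct comparison of influenza status with sIgA is specified nowhere unless titers is read to include it. The binary measures meant are not identified: three in one paragraph, six in another.

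The gap is 6 or 12 announced comparisons without a direct test in the paragraph, depending on which count is intended. No sample size, power figure or efficacy comparison depends on it. The conclusion rests on the protocol text alone; a separate statistical analysis plan, if there is one, was not at hand. It should be corrected, as a secondary-analysis matter.

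**What to change.** Amend the closing paragraph of 9.3.8.2 and the matching synopsis text together:

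- Name the binary outcomes meant, so that three and six no longer conflict.
- For each named outcome, compare log10 HAI (A/Panama/2007/99) and log10 specific nasal sIgA from the Challenge Phase Day 0 sample between subjects with and without the outcome. Use a t-test and Wilcoxon test, or a logistic regression of the outcome on log10 level.
- In the logistic models, say which include antibody, whether sIgA is among the covariates, and which scheduled sample supplies the value, since none falls between the doses.
- The viral-load t-test by influenza status may stay as a separate descriptive analysis, with a note that it partly overlaps with the definition of illness plus infection.

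One caution for reporting: the HAI titer at Challenge Phase Day 0 is also the starting value for the four-fold rise in 9.3.6. The HAI comparison for illness plus infection therefore carries some built-in dependence, which should be stated.

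The cost is one paragraph in two places and 6 to 12 outcome-by-antibody comparisons, without multiplicity correction as in section 9.0. No new samples or visits are needed.
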